### Statistical analyses

Descriptive statistics will be used for all outcome variables at each measurement time to summarise results. Baseline demographic data will be compared (independent *t*-tests and Chi-squared tests) to establish the comparability of groups. An intention-to-treat analysis will be used in which all participants will be analysed in the group to which they were assigned. In addition, sensitivity analyses will also be performed using per-protocol analyses; these analyses will allow to verify the consistency of the results in participants strongly compliant with the interventions (e.g., 75% attendance and home exercises). All dropouts and the reason for dropping out of the study will be reported. Any harm or unintended effects and co-interventions will be recorded. A 2-way ANOVA (2 Interventions [Group-Based or UPC] × 4 Times [0, 6, 12, 26 weeks]) will be used to analyse and compare the effects of the interventions on the primary outcome (Pain Interference Scale) and on four of the secondary outcomes (Pain intensity subscale, EQ-5D-5L, TSK) (SPSS, proc. GENLIN [Generalized Estimating Equations – GEEs]). Effect sizes (Cohen’s *d* for between-groups comparisons, Glass’s Δ for within-group comparisons) will be calculated. Nonparametric Analysis for Longitudinal Data (nparLD Package 2.1, R-software, v.3.6.1) will also be considered in cases where GEEs are not applicable (undefined distributions). If nparLD are used, effect sizes will be reported as relative treatment effect. Satisfaction with treatment will be compared between the two interventions using Chi-squared test for the PASS and Mann Whitney test or independent *t*-tests for satisfaction questions using the Likert scales. Exploratory analyses (using a similar statistical approach as for primary outcome) will be performed to compare the two interventions for each of the four conditions using the region-specific questionnaires (ODI, KOS-ADLS, *Quick*DASH, LEFS).

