### Sample size

Based on our sample size calculation, calculated for our primary outcome (Pain Interference subscale of the Brief Pain Inventory) using data from a pilot study on military members with MSKd [33], 15 participants per diagnosis will be required per group for a total of 120 participants (60 participants/group) (G*Power 3.1.7; α = 0.05, 1-β = 0.95, Baseline mean: 2.9+/− 1.5 points, Follow-up mean: 0.8+/− 1.2 points, expected lost at follow-up = 15% [based on past experiences with this population]. This number will enable us to determine the effects of the interventions for each of the four conditions.

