### Study design and experimental procedures

This pragmatic parallel-group RCT will compare two 12-week interventions and includes four evaluation sessions over 26 weeks (baseline, week 6 [mid-intervention], week 12 [end of intervention] and week 26). Once the written informed consent form will have been signed and eligibility criteria confirmed by an independant PT, participants will take part in the baseline evaluation. At baseline, participants will first complete a questionnaire on sociodemographic, symptoms and comorbidity. Then, they will be randomly assigned to either the 1) group-based supervised training program or 2) usual individual physiotherapy care. They will then take part in their assigned 12-week intervention at the Valcartier Health Centre (Fig. 1). At follow-up evaluations, the primary and secondary outcomes will be assessed using web-based questionnaires integrated within the Research Electronic Data Capture platform (REDCap) [34]. This pragmatic randomized controlled trial protocol have bee registered on clinicaltrials.gov (NCT05235152) [35].

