### Randomisation/blinding

A randomisation list will be established using a computer random number generator (sealedenvelope.com) prior to the initiation of the study by an independent research assistant. Allocation will be concealed in sealed and sequentially numbered opaque envelopes. Randomisation will be stratified by sex and type of MSKd to ensure balance of the treatment groups with respect to these variables. A blocked randomisation (random blocks of 3 or 6) will also be used to make sure that two equal groups of 60 participants (15 participants/diagnosis) will be obtained. Given that for this type of intervention it is impossible to blind the treating PT and participants, only the evaluator and statistician will be blinded. To reduce potential contamination bias, the two interventions will be given in different closed rooms at the Valcartier Health Centre by different PTs. Participants will be instructed to avoid discussing their group assignment or interventions with other participants or with the evaluator.

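### Significance tests on baseline demographics cannot show that randomised arms are comparable; the sentence should be replaced by a descriptive table (minor)

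*Protocol article*

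**What the plan says.** The protocol article, Statistical analyses, says: "Baseline demographic data will be compared (independent *t*-tests and Chi-squared tests) to establish the comparability of groups". The method (tests of difference) and the aim (comparability) are both stated. No margin, size measure or consequence is attached.

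Three other places bear on this:
- Study design and experimental procedures shows that more than demographics is collected before allocation: "At baseline, participants will first complete a questionnaire on sociodemographic, symptoms and comorbidity".
- Randomisation/blinding already controls two variables by design: "Randomisation will be stratified by sex and type of MSKd to ensure balance of the treatment groups with respect to these variables".
- Statistical analyses describes the primary analysis as a two-arm by four-time model, fitted by GEE, with week 0 as one of the times. It names no covariate.

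**The concern.** A test of difference asks whether the data contradict equal population means or proportions. After sound random allocation that null hypothesis is true by design, so the test has nothing to find. A small p-value marks a chance event. A large one does not say that the observed imbalance is small, because no margin is set against which comparability could be judged.

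What matters for the arm comparison is the size of an imbalance times how strongly the variable predicts the outcome. The p-value measures neither. The tests as stated also cover only demographic variables. Symptoms and comorbidity, which are more likely to be prognostic, are collected but fall outside them. Sex, which would be among the demographics, is a stratification factor, so a test on it is nearly empty.

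At stake is the reporting: a table of non-significant p-values may be taken as reassurance it cannot give, and a chance significant one may cast doubt on a sound randomisation.

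**Working it through.** **Inputs.** From Sample size: "α = 0.05, 1-β = 0.95", "Baseline mean: 2.9+/− 1.5 points", "Follow-up mean: 0.8+/− 1.2 points", "expected lost at follow-up = 15" per cent, and "15 participants per diagnosis will be required per group for a total of 120 participants (60 participants/group". Two-sided testing is assumed, since the article does not state sidedness. The number of baseline variables and all correlations are assumptions; the article gives none.

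**1. The plan's own group size.** Pooled SD = √((1.5² + 1.2²)/2) = 1.358. Standardised difference = (2.9 − 0.8)/1.358 = 1.546. A two-sample t-test at two-sided 0.05 and 95% power needs 12 per arm. Allowing for loss, 12/0.85 = 14.1, so 15; and 15 × 4 × 2 = 120. The stated size reproduces, so n = 60 per arm is used below.

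**2. Largest imbalance that passes.** For a continuous variable the limit is t(0.975; 2n − 2) × √(2/n) = 1.980 × 0.1826 = 0.36 SD. For a binary variable split symmetrically about one half:
- 35/60 against 25/60 (58% against 42%) gives chi-squared 3.33, below 3.84, and passes.
- 36/60 against 24/60 gives 4.80 and is flagged.

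**3. False alarms.** With k independent tests the chance of at least one is 1 − 0.95^k: 1 − 0.774 = 23% for k = 5 and 1 − 0.599 = 40% for k = 10. Correlated variables would change these figures.

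**4. What a passing imbalance can do.** Let z be the standardised imbalance and ρ the covariate's correlation with the quantity compared between arms. Given z, the unadjusted test statistic is approximately N(ρz, 1 − ρ²) under no treatment effect, and the estimate is shifted by ρ × imbalance.

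For a comparison of follow-up values alone, at the 0.36 SD limit:

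| ρ (assumed) | Shift, SD | Conditional type I error |
|---|---|---|
| 0.1 | 0.04 | 5% |
| 0.3 | 0.11 | 8% |
| 0.5 | 0.18 | 13% |
| 0.7 | 0.25 | 21% |

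The planned model contains week 0, so its group-by-time contrast compares change, and the relevant ρ is the correlation with change. With equal SDs at both times (a simplification) and a baseline-to-follow-up correlation of 0.5, this is (ρ_follow-up − ρ_baseline)/√(2 × (1 − 0.5)) = ρ_follow-up − ρ_baseline. With ρ_follow-up = 0.5 and z = 1.95:
- ρ_baseline = 0.5: correlation with change 0, error 5.0%
- ρ_baseline = 0.4: 0.1, error 5.3%
- ρ_baseline = 0.3: 0.2, error 6.3%
- ρ_baseline = 0: 0.5, error 12.8%

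If baseline Pain Interference itself differs by 0.36 SD, the change contrast is shifted by (r − 1) × 0.36. That is −0.25, −0.18 and −0.11 SD for r = 0.3, 0.5 and 0.7, with conditional error of 16%, 13% and 10%. The stated tests, on demographic data, would not address that imbalance.

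**5. Averaged over randomisation.** In simulation, type I error is 5.0% for both the follow-up and the change comparison. Restricted to trials whose baseline test was non-significant, it is 3.5% to 4.7%.

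**The case against.** The strongest defence is that this is one descriptive sentence with nothing hanging on it. No covariate, model or analysis set depends on the result, and the primary analysis is the same whatever the tests show. That stands, and it is why the point is minor. It does not rescue the sentence: the purpose is stated, and the method cannot meet it.

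A reader might go further in three ways that the document does not support.
- That the plan treats p > 0.05 as proof of balance. The wording invites this, but no such rule is written.
- That the primary test runs at more than twice its nominal error. The 13% figure needs an imbalance right at the threshold (|z| between 1.90 and 1.96 has a chance of 0.7%), a strongly prognostic variable, and either a comparison that ignores week 0 or a variable unrelated to baseline pain interference.
- That the tests are dangerous because they have low power, especially at 15 per arm within one condition. Power against a true difference is not the issue, since sound randomisation leaves no true difference, and no baseline tests by condition are planned.

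It is also fair to say that a covariate list belongs in the full protocol or analysis plan. Its absence from an article is not held against the trial. Likewise, baseline Brief Pain Inventory scores will be summarised, because descriptive statistics are promised for all outcome variables at each time.

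**Conclusion.** The point holds as a minor error in a stated analysis. Baseline t-tests and chi-squared tests cannot show that randomised arms are comparable. At 60 per arm they pass observed differences of up to 0.36 SD. Over 5 to 10 independent tests (number assumed), they raise at least one false alarm in 23% to 40% of properly randomised trials.

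The primary test is not invalidated, and its overall type I error stays at 5%. Distortion arises only conditionally, when a variable that predicts change is imbalanced, and its size depends on correlations that the article does not give. This rests on two-sided tests at 0.05, the intended 60 per arm, and allocation carried out as described.

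**What to change.** In Statistical analyses:
1. Delete the baseline t-tests and chi-squared tests, together with the clause giving comparability as their purpose.
2. Say instead that baseline data will be tabulated by arm without p-values, covering demographics, symptoms, comorbidity and baseline Brief Pain Inventory scores, and that any imbalance will be judged by its size and likely prognostic weight.
3. State that the arm comparison will include the stratification factors (sex and type of disorder) and a short set of prognostic variables chosen now from those collected at baseline, whatever the table shows. Age and, if the questionnaire records it, symptom duration are examples. To act on change in the two-by-four model, these terms must be allowed to interact with time.

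The third step may sit in the full analysis plan if one exists. The cost is one or two sentences and a few degrees of freedom. The sample size stays at 120 and no new data are needed.

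### The primary GEE analysis relies on a stronger dropout assumption than it needs; a method valid when loss depends on observed scores should lead, backed by a sensitivity analysis for unobserved scores

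*Protocol article*

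**What the plan says.** Four statements in the protocol article bear on this point.

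- **Analysis set** (Statistical analyses): "An intention-to-treat analysis will be used in which all participants will be analysed in the group to which they were assigned".
- **Primary method** (same section): a two-arm by four-visit model for the BPI Pain Interference score, fitted in SPSS by "proc. GENLIN [Generalized Estimating Equations". A nonparametric longitudinal method is the fallback if the distribution makes GEE unsuitable.
- **Expected loss** (Sample size): "expected lost at follow-up = 15% [based on past experiences with this population".
- **Visits** (Study design and experimental procedures): "four evaluation sessions over 26 weeks (baseline, week 6 [mid-intervention], week 12 [end of intervention] and week 26".

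The only sensitivity analysis named is per-protocol, restricted to strongly compliant participants. Dropouts and their reasons are to be reported. The article gives no working correlation, weighting, imputation or missingness assumption. It does not say in so many words that the GEE is unweighted or uses only observed visits; that is the natural reading of what is written.

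**The concern.** Analysing people as randomised does not supply the scores of those who stop answering. With GEE and nothing added, the week-26 comparison draws on those still responding. It is guaranteed consistent only when loss is completely random or depends only on covariates in the model. A correctly specified likelihood model needs less: loss may also depend on scores already observed.

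The design gives reasons to think that loss could follow the scores and could differ by arm. Participants and therapists are unblinded (Randomisation/blinding). Treatment ends early on recovery, on the judgement of each arm's own therapist (Interventions). One arm is treated individually, the other in groups of 5 to 20. Outcomes come by web questionnaire, and the last falls 26 − 12 = 14 weeks after treatment ends. None of this shows that loss will differ by arm, but it makes it possible.

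The stake is the long-term part of the primary objective. The hypothesis is that the group programme does no worse than usual care, so a bias in its favour at week 26 would support that claim directly. The per-protocol analysis does not address this, because it selects on compliance and not on whether outcomes are missing.

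**Working it through.** **1. The plan's own figure.** Inputs from Sample size: "α = 0.05, 1-β = 0.95" and "Baseline mean: 2.9+/− 1.5 points, Follow-up mean: 0.8+/− 1.2 points". Pooled SD = √((1.5² + 1.2²)/2) = √1.845 = 1.358. Standardised difference = (2.9 − 0.8)/1.358 = 1.546. A two-sided two-sample t-test needs 12 per cell (power 0.951). Allowing for 15% loss, 12/0.85 = 14.1, rounded up to 15; 15 × 2 arms × 4 diagnoses = 120. The stated size reproduces. It does so by treating a before-to-after change as a between-arm difference, which is a separate matter and does not affect this point.

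**2. Precision at week 26.** With 15% loss, 60 × 0.85 = 51 per arm. Taking the follow-up SD of 1.2, the standard error of the difference is 1.2 × √(2/51) = 0.238 points.

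**3. Bias under assumed dropout.** Large-sample simulation, 400,000 per arm, true difference 0, 15% monotone loss in each arm.
- From the protocol: the visits, baseline mean 2.9 (SD 1.5), follow-up mean 0.8 (SD 1.2), 15% loss.
- Assumed: means 2.9, 2.2, 1.5, 0.8; SDs 1.5, 1.4, 1.3, 1.2; correlations exchangeable 0.3, 0.5, 0.7 or autoregressive 0.7; log-odds of loss changing by 1 per SD of score; equal loss in both arms.

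Bias in the week-26 difference, in BPI points (range over the four correlation settings):

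| Loss mechanism | GEE independence | GEE exchangeable | GEE unstructured | Likelihood mixed model |
|---|---|---|---|---|
| Completely random | 0 | 0 | 0 | 0 |
| On observed score, same in both arms | 0 | 0 | 0 | 0 |
| On observed score, one arm only | −0.05 to −0.12 | +0.01 to +0.03 | within 0.01 | 0.00 |
| On observed score, opposite by arm | −0.11 to −0.24 | +0.02 to +0.06 | within 0.01 | 0.00 |
| On unobserved score, opposite by arm | −0.19 to −0.28 | −0.05 to −0.14 | −0.07 to −0.14 | −0.09 to −0.15 |

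**4. Agreement with other checks.** A second simulation (2,000 trials, 60 per arm, loss after week 12 depending on the week-12 score, correlation 0.5 to 0.7) gave 0.16 to 0.22 for independence GEE in the opposite-direction case and under 0.01 for the likelihood analysis. A third check, extended to skewed, floor-bounded scores, gave about 0.04 to 0.22 for independence GEE, up to about 0.04 for exchangeable GEE, and under 0.01 for the likelihood model.

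**5. What the sizes mean.** Against the follow-up SD, 0.11/1.2 = 0.09 and 0.24/1.2 = 0.20. Against the standard error, 0.24/0.238 ≈ 1.01. With a bias of b standard errors, a nominal 95% interval covers with probability Φ(1.96 − b) − Φ(−1.96 − b):
- bias 0.24 (b = 1.01): 0.829 − 0.001 ≈ 83%
- bias 0.11 (b = 0.46): 0.933 − 0.008 ≈ 93%
- bias 0.06 (b = 0.25): 0.956 − 0.014 ≈ 94%

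**The case against.** The strongest reply is that the decisive setting is not in the article. Working correlation and imputation are commonly left to a full protocol or analysis plan, neither of which is shown, so their absence is not a fault. With an unstructured working correlation, GEE nearly matches the mixed model even in the opposite-direction case. That stands: the independence figures are an upper scenario, not a forecast. What remains is that the article fixes GEE as the primary estimator, and GEE without weighting or imputation carries the stronger assumption.

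Second, the larger figures need loss to run in opposite directions by arm, which no section predicts. The rule for ending treatment early applies to both arms and ends treatment, not outcome collection. This also stands; one-arm selection halves the bias and equal selection abolishes it.

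Third, a normal mixed model has its own weakness here. The score is bounded at 0, and a normal distribution with mean 0.8 and SD 1.2 puts Φ(−0.8/1.2) = Φ(−0.67) ≈ 25% of scores below 0. The check with skewed, floor-bounded scores kept the likelihood bias under 0.01. The reliance on the mean and covariance model is still a real cost.

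A reader might infer two stronger things. One is that GEE is biased unless loss is completely random. For the between-arm difference that is too absolute, as the second row of the table shows. The other is that a mixed model removes dropout bias. It does so only when loss depends on observed scores and the model is right. When loss depends on unobserved scores it stays biased by 0.09 to 0.15, much like exchangeable or unstructured GEE.

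**Conclusion.** The point holds in a limited form. The named primary method rests on a stronger assumption about loss than the data already being collected require, and the one planned sensitivity analysis does not test it. In the adverse case, where loss follows observed scores differently by arm, the bias ranges from almost nil to about one standard error, depending mainly on a working correlation that the article does not state. All sizes rest on the assumed dropout slope, correlations, intermediate means and SDs, and equal 15% loss. The nil result for equal mechanisms was obtained with a true difference of 0.

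The documents do not support saying that the trial's result will be biased, or that the intention-to-treat sentence is wrong; it only defines analysis as randomised. The change is worth making because it costs little and weakens the assumption, with medium confidence that it would matter in practice.

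**What to change.** Make the primary analysis one of the following:

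- a likelihood-based mixed model for repeated measures with arm, visit and their interaction, unstructured covariance, robust standard errors, and every randomised participant who has any outcome data; or
- the planned GEE after multiple imputation carried out by arm from the baseline, week-6 and week-12 scores.

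Keep the GEE as written as a sensitivity analysis and state its working correlation. Add one simple sensitivity analysis for loss that depends on unobserved scores, for example imputation with a delta shift that may differ by arm.

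The cost is a change of wording and slightly more analysis work. No new data are needed and N remains 120. The downside is reliance on the mean and covariance model for a score with a floor at 0, which the retained GEE helps to check.

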### Outcomes

The primary outcome will be functional limitations, as measured with the Pain Interference subscale of the Brief Pain Inventory – Short Form (BPI). The secondary outcomes will include pain severity as measured with the Pain Severity subscale of the BPI, and health-related quality of life as measured with the EQ-5D-5L. As pain-related fear has been shown to influence outcomes in military members and conservative management reduces pain-related fears [20, 46], both interventions will also be compared on their impact on pain-related fears, measured with the Tampa Scale for Kinesiophobia (TSK) [38]. Furthermore, region-specific symptoms and functional limitations will be assessed using the Oswestry Disability Index (ODI) for low back pain, the shortened version of the Disabilities of the Arm, Shoulder and Hand (*Quick*DASH) for rotator cuff-related shoulder pain, Knee Outcome Survey Activities of Daily Living Scale (KOS-ADLS) for patellofemoral pain syndrome and Lower Extremity Functional Scale (LEFS) for lateral ankle sprain. To monitor compliance with home exercises, participants will be asked to maintain a weekly web-based logbook on RedCap during the 12 weeks of the intervention. Finally, participant’s satisfaction with treatment will be assessed at the end of the treatment (i.e., week-12) (see bellow for further description).

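### The primary model counts baseline as a fourth outcome time, so its intervention-by-time contrast is an unadjusted difference in change scores: unbiased, but less precise than a baseline-adjusted contrast

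*Protocol article*

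**What the plan says.** The primary outcome is one scale for all four conditions: "The primary outcome will be functional limitations, as measured with the Pain Interference subscale of the Brief Pain Inventory – Short Form (BPI". The Study design section gives "four evaluation sessions over 26 weeks (baseline, week 6 [mid-intervention], week 12 [end of intervention] and week 26"), and places the baseline evaluation before random assignment.

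The Statistical analyses section describes a two-way ANOVA that crosses the two interventions with time: "4 Times [0, 6, 12, 26 weeks]) will be used to analyse and compare the effects of the interventions on the primary outcome". It is fitted with "SPSS, proc. GENLIN [Generalized Estimating Equations – GEEs"). The same model serves pain severity, EQ-5D-5L and TSK. Week 0 is thus a level of the outcome factor. No baseline covariate or equal-baseline constraint is mentioned, and the article does not say which term or week carries the primary test.

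Under Randomisation/blinding: "Randomisation will be stratified by sex and type of MSKd to ensure balance of the treatment groups with respect to these variables". The model as stated has two factors, and neither stratification factor is one of them. Baseline demographic data are to be compared by significance tests "to establish the comparability of groups".

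**The concern.** In a two-by-four model with free means, the intervention-by-time term at week t is the arm difference at t minus the arm difference at week 0. Before randomisation the true arm difference is zero, so the subtraction removes no systematic error. It takes out the full chance imbalance at baseline, where the data would support removing only the part that predicts follow-up, and so adds noise.

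If the intervention main effect were the test, it would average a time at which no effect is possible with three at which one is.

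The stake is the width of the confidence interval. The trial's hypothesis is that group training does no worse than individual care, and a wide interval makes that hard to support. The loss carries over to the secondary outcomes that share the model.

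**Working it through.** **Inputs.** From the Sample size section: baseline SD s0 = 1.5, follow-up SD s1 = 1.2, 60 per group, 15% loss, and "α = 0.05, 1-β = 0.95". Evaluable per arm: 60 × 0.85 = 51. The correlation r between baseline and follow-up is not given, so 0.3 to 0.7 is assumed.

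**The plan's own figure.** An SD of √((1.5² + 1.2²)/2) = 1.358 and a difference of 2.9 − 0.8 = 2.1 give d = 1.546. A two-sided two-sample t-test at 0.05 with 95% power needs 12 per group. Then 12/0.85 = 14.1, rounded up to 15, and 15 × 4 × 2 = 120. The stated number reproduces. The 2.1 points are a change over time, so the calculation gives no between-arm target.

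**What the interaction term is.** In 150 simulated complete-data trials of 120 participants, the week-12 coefficient of the two-by-four GEE equalled the arm difference in mean change to about 1e-15.

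**Variance per participant of the arm contrast at one follow-up time.**

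- Change score: s0² + s1² − 2r·s0·s1 = 3.69 − 3.6r
- Baseline-adjusted: s1²(1 − r²) = 1.44(1 − r²)
- Ratio if the SDs were equal: 2/(1 + r)

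**Detectable difference**, two-sided 0.05, 95% power: (1.960 + 1.645) × √(2 × variance/51).

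| r | Change variance | Adjusted variance | Ratio | Ratio, equal SDs | Detectable, change | Detectable, adjusted |
|---|---|---|---|---|---|---|
| 0.3 | 2.61 | 1.31 | 1.99 | 1.54 | 1.15 | 0.82 |
| 0.5 | 1.89 | 1.08 | 1.75 | 1.33 | 0.98 | 0.74 |
| 0.7 | 1.17 | 0.73 | 1.59 | 1.18 | 0.77 | 0.61 |

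With the protocol's SDs, a baseline-adjusted analysis would match the change-score precision of 102 evaluable participants with about 51, 58 or 64 (102 divided by the ratio). Follow-up scores alone have variance 1.2² = 1.44, so for r below (3.69 − 1.44)/3.6 = 0.625 the change score is less precise than ignoring baseline altogether.

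The simulation at r = 0.5 agrees: mean standard error 0.247 for the two-by-four GEE and 0.189 for the baseline-adjusted model (formula with 60 per arm: 0.251 and 0.190).

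**Main effect.** A constant effect δ averaged over four times is (0 + δ + δ + δ)/4 = 0.75δ.

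**Stratification factors.** Mean standard errors from the same simulation, under assumed diagnosis effects:

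| Diagnosis affects | 2 × 4 GEE | + strata, main effects | + strata by time | Baseline-adjusted | Baseline-adjusted + strata |
|---|---|---|---|---|---|
| level only | 0.247 | 0.247 | 0.242 | 0.198 | 0.188 |
| level and change | 0.259 | 0.259 | 0.244 | 0.230 | 0.190 |

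Strata entered only as main effects leave the interaction unchanged, because differencing already removes anything constant over time. They help in a baseline-adjusted model or as strata-by-time terms.

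**The case against.** The strongest reply is that nothing here makes a conclusion wrong. The change-score contrast is unbiased under randomisation, and its loss depends on a correlation that the article does not give and on pilot SDs that fall from 1.5 to 1.2. With equal SDs the variance ratio is 1.5 to 1.2. The article also gives no between-arm target or margin, so it cannot be shown that about 0.24 points (0.98 − 0.74) would alter a decision. All of this stands. It limits the size of the point but does not remove it, because the adjusted contrast is more precise at every correlation examined.

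It can also be said that covariate lists belong in an analysis plan that is not shown. That holds for sex and type of disorder, whose absence from a condensed article is no finding in itself. It does not hold for week 0, which the article expressly places among the outcome times.

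A reader might infer that leaving out the stratification factors makes the planned standard errors too wide, for instance by 3 to 12% from 1/√(1 − R²) with R² of 5 to 20%. The documents give no such R², and the formula belongs to a baseline-adjusted model. In the stated model, main effects for the strata change nothing in the interaction with complete data.

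The baseline significance tests concern demographic data and no analysis depends on them. They are a reporting matter only.

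**Conclusion.** The point holds as a loss of efficiency in a stated method. If the intervention-by-time term is the test, its variance is about 2.0 to 1.6 times the baseline-adjusted variance for correlations of 0.3 to 0.7 with the protocol's SDs, or 1.5 to 1.2 times with equal SDs. The figures assume one follow-up time, 51 evaluable per arm and a common correlation in both arms. If the main effect is the test, the problem is instead dilution of a constant effect to three quarters. Only one of these two consequences can apply to the primary test, and the article does not say which.

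A reader might go further and conclude that the planned analysis is biased or invalid. The documents do not support that. How much the stratification factors could add cannot be determined from the article.

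**What to change.** Preferred: keep all randomised participants in a longitudinal model of weeks 0, 6, 12 and 26, with the arm means constrained to be equal at baseline. Use a mixed model with unstructured covariance, or a GEE whose working correlation is not independence; under independence the constraint yields only the follow-up comparison, with variance 1.44.

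Alternative: model weeks 6, 12 and 26 with baseline BPI Pain Interference by time as a covariate. This drops participants who have baseline data only, which should be stated against the intention-to-treat commitment.

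In either form, include sex and type of disorder, by time in the constrained-baseline form. Adding them only as main effects to the present two-by-four GEE would not help the interaction. Take the treatment effect from the arm contrast at one named week. Use the same form for BPI severity, EQ-5D-5L and TSK. The baseline demographic comparison can be a descriptive table.

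The cost is analysis wording. No new data are needed and the planned 120 participants are unaffected.
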